#### **8.5.3 Safety Population**

In both Part 1 and Part 2, all patients who sign informed consent and receive at least one dose of study drug will be included in the Safety population (Safety Set).

### **8.6 Safety Endpoints**

The safety analyses will be performed on the Safety Set. Study-procedure-related SAEs (only) will be recorded for patients who sign informed consent and receive at least one dose of study drug. Safety analyses will include all data available at the time of database lock. After the last database lock, follow-up information on SAEs and newly reported related SAEs will be managed through the Pharmacovigilance database.

To investigate dose response, safety parameters will be tabulated by cohort. Patients who demonstrate evidence of tumor response (CR, PR, SD) by physical examination or radiographic study and/or improvement of symptoms may receive Extended Treatment,

which may bias the assessment of dose response. Exploratory analyses to examine the relationship between dose, duration of treatment, and safety parameters will be undertaken.

Safety assessments to be summarized are:

- AEs
- DLTs
- Changes in clinical laboratory assessments from pre-treatment to study visits
- Change in vital signs from pre-treatment to study visits
- Changes in physical examination from pre-treatment to study visits
- Evaluation of development of antibodies to GC1008

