### **3. STUDY OBJECTIVES**

#### **3.1 Part 1, Dose Escalation**

##### **3.1.1 Primary Objective**

- To assess the maximum tolerated dose (MTD), dose-limiting toxicity (DLT), and safety of GC1008 in patients with locally advanced or metastatic renal cell carcinoma or malignant melanoma.

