Dose modification for an individual patient in either the first or second cohorts of Part 2 will be allowed provided the treatment is first discussed and agreed upon with the Sponsor and follows the general guidelines provided below. Treatment delays will be allowed. However, delays of >56 days (8 weeks) between scheduled doses will result in patient withdrawal from study treatment. Replacement of patients with treatment delays of >56 days (8 weeks) will be managed as described below.

During the patient expansion, all SAEs will be reported to the Sponsor. Safety will be monitored continuously, and all safety data will be reviewed with the DMC on a quarterly basis. At any time, an emerging safety profile of concern may result in modification of the study.

---

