## 7.2 Adverse Events

At each study visit, patients will be evaluated for new or evolving AEs. The physician should elicit symptoms using an open-ended question, followed by appropriate questions that clarify the patient's verbatim description of AEs or change in concomitant medications. A review of systems will be performed.

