### **8.6.1 Adverse Events**

AEs will be classified using a current version of the MedDRA coding dictionary. All reported AEs will be displayed in patient listings. The safety assessment will be based on the incidence of treatment-emergent AEs, including summaries of SAEs, treatment-limiting toxicities, AEs leading to withdrawal, and AEs deemed related to study treatment. The severity of each AE will be assessed using the NCI CTCAE Toxicity Scale, Version 3.0, dated 12 December 2003, Appendix C. If CTCAE does not apply, criteria in described above will be used.

AEs will be categorized and tabulated by system organ class, preferred term, intensity, seriousness, outcome, and relationship to study treatment. Additionally, discontinuations due to AEs, will be summarized. Information collected prior to GC1008 treatment will be presented separately from treatment-emergent signs and symptoms.

If a patient has more than 1 occurrence of an AE for a specific preferred term, the patient will be counted only once for that preferred term. The most intense occurrence of an AE, as well as the most extreme relationship of the AE to the study treatment, will be indicated in cases of multiple occurrences of the same AE.

Changes from pre-treatment in clinical laboratory tests will be summarized. The analysis of laboratory values will also be based on frequencies of abnormal values. Safety outcomes information will be handled by providing counts and percentages if categorical, and by

providing univariate descriptive statistics if continuous. Genzyme will provide cumulative data (as specified in the DMC charter) to the DMC for review.

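### Section 8.6 limits SAE recording in dosed patients to study-procedure-related events, which contradicts the protocol's other SAE rules and should be corrected

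*Protocol*

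**What the plan says.** Section 8.6 names the analysis population: "The safety analyses will be performed on the Safety Set". It then gives the recording rule at issue: "Study-procedure-related SAEs (only) will be recorded for patients who sign informed consent and receive at least one dose of study drug". The next sentence reads: "Safety analyses will include all data available at the time of database lock".

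Section 8.5.3 defines that population. In both parts, "all patients who sign informed consent and receive at least one dose of study drug will be included in the Safety population".

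Safety is part of the primary objective in Part 1 (Section 3.1.1: "To assess the maximum tolerated dose (MTD), dose-limiting toxicity (DLT), and safety of GC1008") and is the primary objective in Part 2 (Section 3.2.1).

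Other sections treat SAEs more broadly. Section 4.1.2 says: "During the patient expansion, all SAEs will be reported to the Sponsor". Section 8.6.1 says: "The safety assessment will be based on the incidence of treatment-emergent AEs, including summaries of SAEs". Section 5.3, the footnotes to the main schedule of events (Table 7-1) and Section 7.2.1 add rules on follow-up windows and on DLTs, which are compared below.

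**The concern.** The word in parentheses makes the limit explicit, and the limit is attached to the patients who were treated. Taken at its word, the rule leaves out an SAE caused by GC1008, an SAE from the underlying cancer and an SAE of unknown cause. These are the events that a Phase 1 safety objective exists to count.

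The analysis cannot make good a recording rule of this kind: a tabulation can be rerun, but an event that was never recorded cannot be recovered from the database. Safety data also drive a decision within the trial. Under Section 4.1.2, whether a second Part 2 cohort is enrolled, and at which of the two planned dose levels, depends on the review of available safety data by the sponsor and the DMC. Anyone drafting CRF guidelines or dataset specifications from Section 8.6 would find a clear instruction that conflicts with the rest of the protocol.

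**Working it through.** No power, rate or interval is involved. The check is a comparison of wording.

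**Step 1: whom the limit covers.** Section 8.6 limits recording for patients who meet two conditions: consent, and at least one dose. Section 8.5.3 builds the Safety Set from the same two conditions. The groups are identical, so the limit covers 100% of the safety analysis population. On the protocol's own counts, that is 22 treated patients in Part 1 plus 6 planned in Part 2 with one cohort, or about 12 with two: 22 + 6 = 28, or 22 + 12 = 34. These are patients under the literal rule, not events lost.

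**Step 2: whether the sentence has an escape.** It sets no time limit, so it cannot be read as covering only the days between consent and first dose. It requires dosing, so it cannot be read as covering only undosed patients.

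**Step 3: the other rules side by side.**

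| Place in protocol | Patients and period | SAEs covered |
|---|---|---|
| 8.6 | Consented and dosed, no period given | Procedure-related only |
| 4.1.2 | Part 2 | All, reported to the sponsor |
| 5.3; Table 7-1 footnote 6 | Withdrawn patients, to 45 days after last dose | New AEs and SAEs of any cause |
| 5.3 | Withdrawn patients, after 45 days | Those possibly caused by GC1008 |
| Table 7-1 footnote 10 | After the End-of-Treatment Visit | Those possibly caused by GC1008 |
| 7.2.1 | Part 1, first 28 days | DLTs, collected through SAE reporting |
| 8.6.1 | Safety analysis | SAE summaries; AEs tabulated by seriousness and by relationship to treatment |

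**Step 4: whether they can all hold.** They cannot. Two of the three DLT categories in Section 7.2.1 require a causal relation to GC1008. A table by relationship to study treatment needs drug-related events to have been recorded. The late-reporting rules ask for possibly drug-related SAEs even after the main window closes, which makes no sense if such events were not recorded inside it.

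**Step 5: how the contradiction divides by part.** The explicit all-SAE rule in Section 4.1.2 is for Part 2. For Part 1 the contradiction rests on Sections 5.3, 7.2.1 and 8.6.1 and on the Table 7-1 footnotes. Section 7.2 ("At each study visit, patients will be evaluated for new or evolving AEs") gives only indirect support, because it concerns how AEs are elicited and does not say which SAEs are recorded.

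**The case against.** The strongest reply is that nobody would follow this sentence. The very next one takes in all data available at lock. Section 8.6 goes on to route related SAEs first reported after the last lock to the pharmacovigilance database, which presupposes that related SAEs were captured before it. Table 7-3 marks SAE and AE assessment at every Extended Treatment visit. Part 1 treatment is complete, with no DLT in 22 patients, and Part 2 has an explicit all-SAE rule.

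Much of this stands. It limits what can be claimed in three ways:

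- A reader might infer that drug-related SAEs were, or will be, missing from the primary safety result. The documents do not support that, because the surrounding sections require or presuppose wider collection.
- A reader might want a number of excluded SAEs. The protocol gives no SAE rate, so any such figure would rest on an assumption with no source.
- A reader might infer that consented but undosed patients have no SAE rule. That cannot be established, because the main schedule of events is not legible in the available copy and some text refers to material not shown there.

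The reply does not rescue the sentence itself. Including all available data helps only for data that were recorded. An explicit restriction in the section governing the safety analysis should not depend on readers ignoring it.

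**Conclusion.** The sentence in Section 8.6 is wrong as written and must be corrected. It applies a procedure-related-only limit to the entire Safety Set and contradicts at least four other places in the protocol, on data that serve the primary objective of both parts.

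It is an internal contradiction in a recording rule, most likely a drafting error, and not evidence of lost data. The likely explanation is that the limit was meant for consented patients before or without a first dose and that the Safety Set wording was carried into it. The protocol does not say so; this is an inference. The finding itself rests only on the identity of the two patient groups and on the comparison of rules, and needs no assumed event rate.

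**What to change.** Reword the sentence in Section 8.6 so that the procedure-related-only limit does not apply to patients who have received GC1008. The sponsor should confirm which patients and which period it was meant for, and state them.

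Add that, for the Safety Set, AEs and SAEs of any cause are recorded and summarized within the reporting windows of Section 5.3 and the Table 7-1 footnotes, and that after those windows only SAEs possibly related to GC1008 are reported. The windows need to be cited, because an open-ended promise to record everything would contradict the late-reporting rules. They also differ: 45 days after the last dose for patients who withdraw, and up to the End-of-Treatment Visit otherwise. On the planned schedule the last dose falls on Day 56 (28 + 14 + 14) and that visit on Day 140, so the second window is 140 − 56 = 84 days.

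Check that the CRF completion guidelines did not copy the limit. If they did, compare the SAE entries for dosed patients with the pharmacovigilance database before lock.

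The cost is a correction to one sentence, one added statement and one document check. The correction itself needs no new data, added patients or change to the planned analyses.

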If the safety profile of this agent permits, patients who demonstrate evidence of SD or tumor response (CR or PR) by Day 140 (End-of-Treatment Visit) may be offered Extended Treatment with GC1008 at the same dose they previously received, the current safe dose (the highest dose in which 0 of 3 or ≤1 of 6 patients experienced a DLT) or, if known, at the MTD or maximal safe dose.

Following completion of GC1008 treatment, patients will be asked to continue into long-term follow-up. Patients eligible for long-term follow-up include all patients who received GC1008 and meet criteria as outlined below. Long-term follow-up visits will occur every 3 months for up to 2 years or until 1 of the criteria is met. If a response occurs during long-term follow-up, efficacy assessment(s) will be evaluated by the Investigator to document a confirmed response.

Genzyme will provide ongoing safety monitoring and a DMC, consisting of 2 oncologists, will review safety data on a regular basis. Safety will be monitored by AE assessments, physical examination, vital signs, and clinical laboratory tests. Cumulative safety data will be prepared for DMC review at least every 3 months to assess any safety signals or trends. Safety issues that arise out of such reviews may lead to modifications of the treatment program.

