## **4.2 Patient Assignment and Identification**

This is an open-label study. Patients will be enrolled and assigned to a treatment cohort only after they provide written informed consent, complete all pre-treatment assessments, and meet all requirements of the inclusion and exclusion criteria. The dosing cohort, patient identification number, and patient weight will be recorded in the electronic case report form (eCRF) and on the Drug Accountability Log, and study treatment infusion will be prepared accordingly.

A detailed description of patient identification is provided in the Study Operations Manual. All patients who provide written informed consent will be documented in the Patient Screening Log.

---

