In general, a patient experiencing a DLT in Part 1 will not receive additional GC1008 and will be withdrawn from the study. However, if upon review, Genzyme, the PI, and the DMC find that the study drug could continue with a reasonable margin of safety, treatment may be reinitiated at the same dose-level and the patient can be allowed to complete the course of GC1008 and continue on-study.

If a patient withdraws from the study after receiving GC1008, in either Part 1 or Part 2, the investigator should make every effort to perform a final assessment using the procedures set forth in the End-of-Treatment Visit, except as noted in Table 5-1. A final assessment should be performed within 30 days after withdrawal. Patients who withdraw from the study will be followed for new AEs and SAEs for 45 days after their last dose of GC1008, as outlined above. After the 45-day follow-up period, any SAE that comes to the attention of the site staff that may be causally related to GC1008 (i.e., there is a reasonable possibility that the event may have been caused by the drug) should be reported to Genzyme.

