### 6.2.2.2 Dose Reduction (Part 2 Only)

In Part 2, all dose reductions should first be discussed between the Investigator and Sponsor. (No dose reductions were allowed in Part 1.)

If a patient in Part 2 develops worsening symptoms associated with skin events following re-treatment at the same dose level that are grade 3/4 (with the exception of new grade 3 skin cancers) or are intolerable, the dose may be dropped one dose level following a treatment break where symptoms improve to  $\leq$  grade 2 and become tolerable. For patients initially receiving GC1008 at 15 mg/kg, the dose will be reduced to 10 mg/kg, and for patients initially receiving GC1008 at 10 mg/kg, the dose will be reduced to 3 mg/kg. Only one dose level reduction is allowed per treatment course.

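### The by-cohort safety dose-response table on all data at lock can show events from a later, different dose or from longer exposure under the assigned dose

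*Protocol*

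**What the plan says.** Protocol Section 8.6 sets the grouping, "To investigate dose response, safety parameters will be tabulated by cohort", and the data window: "Safety analyses will include all data available at the time of database lock". Section 4.2 fixes cohort membership at entry: "Patients will be enrolled and assigned to a treatment cohort only after they provide written informed consent".

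The dose can change afterwards.
- **Part 1.** Under Section 4.1.1 (text after Table 4-1), patients with stable disease or response may be extended "at the same dose they previously received, the current safe dose" or, "if known, at the MTD or maximal safe dose". Section 4.1.2 reports that the maximum safe dose was 15 mg/kg.
- **Part 2.** Section 6.2.2.2 allows individual reductions: "For patients initially receiving GC1008 at 15 mg/kg, the dose will be reduced to 10 mg/kg", and from 10 to 3 mg/kg for those who started at 10 mg/kg.

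Section 6.1 allows up to two further courses. Section 8.6.1 counts a patient once per preferred term and shows the most intense occurrence. Section 8.6 itself warns that Extended Treatment can bias the dose-response assessment, and it promises exploratory analyses of dose, treatment duration and safety. It says nothing there about Part 2 reductions.

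**The concern.** A table meant to show dose response should group events by a dose that the patient was receiving. Here the grouping is fixed at entry while the data run to lock, and the protocol allows both dose and exposure to change in between. The worst-grade rule adds to this: a mild event at the assigned dose followed by a severe one at a higher extended dose is shown as severe under the lower dose.

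If risk rises with dose, carrying higher-dose events into lower cohorts flattens the gradient. Extension at the same dose raises crude incidence in whichever cohorts have patients who benefit, so the direction of that part is unpredictable. The table matters beyond Part 1, because Section 4.1.2 says Part 2 should help define dose levels and schedule for a Phase 2 study.

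**Working it through.** The plan states no figure for this point, so none can be reproduced. The check compares sections and then illustrates size under stated assumptions.

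**1. Which events can be misplaced**

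| Event | Dose at onset | Shown under | Correct? |
|---|---|---|---|
| DLT (28 days after first dose, Section 7.2.1) | assigned | assigned cohort | yes |
| Part 1, course 1 | assigned | assigned cohort | yes |
| Extension at same dose | assigned | assigned cohort | dose yes, exposure longer |
| Part 1 extension at higher dose | higher | assigned cohort | no |
| Part 2 before reduction | starting | starting cohort | yes |
| Part 2 after reduction | reduced | starting cohort | no |

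**2. Can a higher dose be available at Day 140?** Escalation waits 28 days after the last patient in a cohort receives the first dose (Section 6.2.1). With no enrolment delay and no cohort expansion, the time from the start of a cohort until 15 mg/kg has cleared its 28 days is 28 × (number of cohorts from that one to the sixth):
- 0.1 mg/kg: 28 × 6 = 168 days, which is later than Day 140.
- 0.3 mg/kg: 28 × 5 = 140 days, with no slack.
- 1 mg/kg: 28 × 4 = 112 days, with 28 days of slack.
- 3 mg/kg: 28 × 3 = 84 days, with 56 days of slack.
- 10 mg/kg: 28 × 2 = 56 days, with 84 days of slack.

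A switch to 15 mg/kg at first extension is thus plausible for the middle and upper cohorts (15/1 = 15-fold, 15/3 = 5-fold, 15/10 = 1.5-fold). For the lowest cohort it needs the 35-day allowance before extension (Table 7-3, footnote 1; 140 + 35 = 175 days) or a later course.

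**3. Exposure alone.** Each course has 4 doses (Tables 4-1 and 7-3), so a patient may receive 4, 8 or 12. With an assumed constant per-dose risk p, P(at least one event in k doses) = 1 − (1 − p)^k:

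| p (assumed) | 4 doses | 8 doses | 12 doses |
|---|---|---|---|
| 0.02 | 7.8% | 14.9% | 21.5% |
| 0.05 | 18.5% | 33.7% | 46.0% |
| 0.10 | 34.4% | 57.0% | 71.8% |

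**4. Dose change plus exposure.** Assume a low-dose cohort of 3 with one patient extended, per-dose risk q0 at the assigned dose and q1 in extension, and m extra doses. Expected cohort incidence = {2[1 − (1 − q0)^4] + [1 − (1 − q0)^4 (1 − q1)^m]} / 3.

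| q0, q1 (assumed) | Course 1 only | m = 4 | m = 8 |
|---|---|---|---|
| 0.02, 0.02 (same dose) | 7.8% | 10.2% | 12.4% |
| 0, 0.05 | 0% | 6.2% | 11.2% |
| 0.02, 0.05 | 7.8% | 13.5% | 18.1% |
| 0.02, 0.10 | 7.8% | 18.3% | 25.3% |

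The first row is exposure without a dose change: (2 × 0.0776 + 0.1492)/3 = 10.2% and (2 × 0.0776 + 0.2153)/3 = 12.4%. For the 0.02, 0.05 row with one extra course, exposure alone accounts for 10.2 − 7.8 = 2.4 points of the rise, and the higher dose for a further 13.5 − 10.2 = 3.3 points.

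**The case against.** The best defence is that Section 8.6 already names the Extended Treatment bias and plans analyses of dose and duration. Detailed methods are left to an analysis plan that is not shown and may set a dose-at-onset rule. All events are also listed by patient, and grouping by assigned cohort is a recognised descriptive convention. Much of this stands: the bias was noticed, and the remedy is a modest one. But the protocol itself fixes both the grouping and the data window of the table it uses for dose response, and exploratory analyses do not change that table. Efficacy, by contrast, is analysed by dose administered (Section 8.5).

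A reader might infer three stronger things that the documents do not support.
- **That the dose selection is compromised.** Escalation used first-dose DLTs within 28 days, before any extension or reduction. That step is complete, with no DLTs in 22 patients.
- **That the typical error is a 150-fold jump from 0.1 to 15 mg/kg.** Step 2 of the working shows this is close to unreachable at first extension.
- **That patients who stop early are observed for only 45 days, against 84 for completers (Day 56 to Day 140).** Section 5.3 does say "Patients who withdraw from the study will be followed for new AEs and SAEs for 45 days after their last dose of GC1008". The same section keeps patients removed from treatment under safety and outcome follow-up, with exceptions, and follows discontinuers every 3 months. No firm follow-up contrast can be drawn from the 45 days alone.

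On Part 2, a reduction follows worsening symptoms after re-treatment at the same dose, so the triggering event is already credited correctly. Only later events are in question, and some of those may be delayed effects of the higher dose.

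**Conclusion.** The concern holds in a limited form. Followed as written, the plan can place higher-dose or longer-exposure events under a lower-dose cohort in its safety dose-response table. It recognises part of this without correcting the table, and it leaves Part 2 reductions unmentioned. The illustrated shift, from 7.8% to between 13.5% and 25.3% in a cohort of 3, assumes that one patient is extended at a higher dose, a constant per-dose risk of 2% at the low dose and a risk of 5% to 10% at the higher dose. None of these is given in the protocol. If no patient changed dose, only the exposure part remains.

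The first study report is triggered when all patients have finished one course or discontinued (Section 8). This limits the extended data at that lock but does not exclude them, since Part 1 patients may have been extended earlier.

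**What to change.** Change the analysis text only:
1. Make the by-cohort dose-response safety table course 1 only, from first dose to the earlier of the first Extended Treatment dose or the Day 140/End-of-Treatment Visit. Show the number of doses and follow-up time per cohort, because early leavers will still have less of both.
2. Tabulate Extended Treatment events separately, by dose received at onset, with exposure.
3. Flag events in Part 2 patients after a dose reduction, giving both the starting and the current dose.
4. Keep the all-data by-cohort table as supportive.

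The window should not end 45 days after the last course-1 dose. That would be Day 45 for a one-dose patient and Day 56 + 45 = Day 101 for a completer, and it would drop the Day 140 skin assessment (Table 7-2).

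The cost is analysis text and programming, with no change to visits or to any clinical rule. The downside is that later events sit in a second table, and some delayed effects of an earlier dose may be shown under the later one.
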